**1. Aims of the project**

The primary aim of this study is to increase timely diagnosis of dementia through an evidence-based intervention promoting memory service access. We will test in a randomised controlled trial if this intervention increases the number of people with undiagnosed dementia presenting with memory related problems to their GP; the number of patients GPs refer appropriately to memory services; and if this referral is at an earlier stage. We are currently collaborating with the Alzheimer’s Society and their reference groups (including the GP reference group) to redesign the evidence-based CHOICE leaflet1 to ensure usability, acceptability and relevance, and to develop a personal letter from GPs to the “at risk” population to accompany the leaflet.

Research questions

Does sending a leaflet1 on how to overcome barriers to accessing help for dementia to people aged over 70 registered in a general practice, with an accompanying personal letter from the GP, lead to people with dementia presenting earlier to specialist dementia services compared with usual care over 12 months, and if so is it at low cost? We will test the hypotheses that over 12 months people receiving the intervention will present earlier (mean of 3 points higher on MMSE score)2 than those not receiving it and that the costs of the intervention are small.

Primary objective

To enable people with dementia to receive an earlier diagnosis

Secondary objectives

1. To increase the number of people with dementia receiving diagnoses
2. To increase the numbers of people with memory problems presenting to GPs.
3. To calculate the cost-effectiveness of the intervention considering the cost of implementing the CHOICE intervention and the numbers of appropriate and inappropriate referrals to memory services.

**2. Work which has led up to the project**

Why early diagnosis of dementia needs to be increased

The number of people aged >65 will increase by 15%, and those >85 years by 27%, over the next decade3. Thus the 820,000 people currently living with dementia in the UK4 is rising, as dementia prevalence doubles with every five-year increase in age-band5,6. The UK Dementia Strategy7 promotes timely diagnosis (diagnosis made earlier in the disease trajectory) of dementia.

Family carers often experience difficulty in obtaining a diagnosis of dementia for their relative, which can take several years, and the delay results in increased anxiety and carer burden7,8,9. Families report that relatives with memory problems are reluctant to consult their GP about their memory and deny problems when seen1. Other barriers to seeking helpinclude fear of the diagnosis, concerns about stigma, GP reluctance to make this diagnosis, and negative responses from other family members1,7,10,11.

People with dementia and carers usually feel relieved by diagnostic certainty and can access treatment with potentially better results, start to plan and make choices, and play a more active role in their current and future health care1,11,12. Early diagnosis and intervention in dementia facilitates access to specialist services, support and treatment, and is cost-effective9,10,13,reducing crises and delaying care-home admission9,13. Memory services have positive effects on the quality of life of people with dementia and treat neuropsychiatric symptoms which are the most common predictors of institutionalisation13,14,15. Care-home placement costs the UK £7 billion/year, with two-thirds paid for by tax and one-third in private funding6,10,13. The Croydon Memory Service model estimates that a 10% reduction in care home admissions over 10 years, through improving access to memory services for early dementia diagnosis and intervention, could result in savings of £120 million in health and social care expenditure and £125 million in private expenditure per year, with gains of 6,250 QALYS13.

The All-Party Parliamentary Group on Dementia (APPG)16 found that despite the emphasis in UK national policy’s on early and increased diagnosis in dementia, there has been little progress over the last few years17, comparing poorly with other European countries10,18. Conversely, huge geographical variation exists within the UK for diagnostic rates in dementia, suggesting it is possible to increase diagnosis19.

Previous work to increase early diagnosis of dementia

We are building on earlier work which improved GP knowledge about dementia and specialist services7,8,9,10. GPs know about dementia, but may lack experience and confidence in diagnosing it and informing patients8,9,10,20. Despite attempts, including education and financial incentives, to improve diagnosis of dementia in UK primary care, detection remains low even after presentation9,10,21, partly as early diagnosis can be difficult23,24. Community based campaigns about seeking help for memory problems are insufficient by themselves to ensure adequate early diagnosis of dementia25. The Alzheimer’s Society previously funded a community based leaflet campaign to increase awareness and presentation of people with dementia to GPs, which was unsuccessful in increasing diagnosis. Previous interventions have neither specifically targeted older people nor engaged the GP, nor used the relationship, nor addressed barriers to diagnosis other than symptom recognition.

The current intervention

Our intervention follows the Medical Research Council guidelines for development and evaluation of complex interventions26,27. We are building on peer reviewed, published qualitative work which identified the patient and healthcare barriers to early presentation with dementia and developed an intervention to engage patients and carers to improve early presentation1. Our work translates research findings into practice and tests the implementation of an existing evidence-based intervention. The intervention is currently being further developed by us in collaboration with the Alzheimer’s Society GP reference group and staff including dementia advisors; people with dementia patients and family carers and will be ready for testing if this grant is funded. These leaflets remain available to all28, but our intervention will target people to whom they are relevant and ensure they receive them. It aims to help both the person with memory problems and their families to overcome common barriers to seeing their GP after identifying symptoms of dementia. In addition, it delineates strategies to encourage GPs to refer the person with memory problems on for specialist assessment, where appropriate, in response to a relative’s or patient’s concerns about a patient’s memory loss.

GP personal letters with information leaflets changed patient’s behaviour in the field of cancer. In bowel cancer, such letters led to a massive increase in uptake of a difficult screen, involving a self administered enema at home, followed by endoscopy at clinic29. This study will test these methods, which have been successfully implemented in cancer research to raise awareness and increase presentation within the general population. Cancer and dementia are both terminal diseases in which early detection and diagnosis allow access to treatment and services. In cancer, early detection and treatment can be curative, or increase lifespan. While currently dementia is incurable, early diagnosis means the ability to plan ahead11,12, to receive treatment to reduce the cognitive and neuropsychiatric symptoms associated with dementia, improve quality of life7 and delay institutionalisation13,18.

Why this Alzheimer’s Society call is the right place to fund our study

The Alzheimer’s Society (AS) has identified ‘Getting a Diagnosis’ as one of the priority “Challenges facing primary carers for people with dementia”30.Our study sits alongside the AS campaign to increase diagnosis and adds value at a relatively low cost. The project targets many of the barriers (e.g. patients refusing a referral, techniques to persuade a patient to accept help, relative’s giving history of memory loss, leaflets aimed at family carers) identified in the AS consultation. The Alzheimer’s Society consumer groups, including GPs and carers, are working collaboratively with us, and the AS designers, in developing the intervention from the research base to practice. It engages the AS uniqueresources of consumers and dementia experts. This joint project fits with the AS research priorities and with its aim to give evidence based advice31.By assisting people to recognise dementia and seek appropriate help we are equipping people to play a more active role in their health care. Improvements in health will be demonstrated by the increased uptake of diagnostic services for people with memory problems. This is an innovative and simple change in practice and currently no such approaches are known to have been tried within dementia to encourage an improvement in the number of people with dementia receiving a diagnosis. [name] (Dementia “Tsar”) indicates that the Department of Health will support adopting the intervention for wider dissemination if it is successful (“120%”).

**3. Detailed experimental design and methods to be used in investigating the problem**

The study will be a pragmatic, multi-site, cluster randomised controlled trial in which the intervention and treatment as usual group will be compared in terms of cognitive severity at diagnosis. The intervention is a personalised letter from their GP and leaflet (see figure 1 below). The leaflet contains information about overcoming common barriers to accessing dementia diagnosis care if people are concerned about a relative or themselves1.

It covers:

- How to persuade someone to go to the doctor if they or their family are worried about their memory.
- What to do if the GP can’t see there is a problem
- What to do to be referred to specialist services
- What to do to prevent the doctor being unable to talk to you about your relative because of confidentiality
- What to do if the person with memory problems refuses help
- What information patients and families can get about the illness
- What to do if things are not working
- Help available for carers

**4. Study population**

We will include all registered patients within GP practices over the age of 70 years who do not currently have a diagnosis of dementia, live in a care home or have been referred to specialist memory services.

[figure not shown]

KEY

Problems experienced

Outcomes measured

[figure not shown]

**Referral to memory service**

**Figure 1 Project plan for facilitating early diagnosis in dementia**

**5. Recruitment sites**

The research will take place in UCLPartners partnership trusts where our team work clinically. The partnership consists of UCL and the local primary and secondary care trusts including mental health trusts: Camden and Islington NHS Foundation Trust, North East London NHS Foundation Trust, North Essex Partnership NHS Foundation Trust and Barnet Enfield and Haringey Mental Health Trusts. [name] is the dementia lead for UCLPartners and a collaborator on the project. UCLPartners have agreed collaboration and the sites are geographically accessible. The project fits with UCLPartners’ dementia strategy with which all participating trusts are engaged. UCLPartners will help facilitate the engagement of commissioners to fund additional activity within the memory services if necessary. We will also approach surrounding counties to London to recruit GP practices if needed, such as Hertfordshire, Essex, Kent, Surrey and Berkshire. Sites are diverse in socioeconomic status, ethnic composition, and are inner-city to rural. This covers the variation within England enabling our results to be externally valid. [name] a co-applicant is a research active GP as is [name] who is a collaborator. The recruitment of GP practices will be facilitated through Dementia and Neurodegenerative Diseases (DeNDRoN), the Primary Care Research Networks (PCRN) and Alzheimer’s Society GP Reference Group.

**6. Patient, service and public involvement**

A family carer from the Alzheimer's Society Research Network helped develop the protocol and she will be a member of the Trial Steering committee. We will consult further on the design and content with the Alzheimer’s Society GP reference group and through focus groups with Alzheimer’s Society including dementia advisors; dementia patients and carers, and consult iteratively about changes in the materials from September 2012 over the following five months. An Admiral Nurse, representing the voluntary sector organisation Dementia UK is a collaborator and will be a member of the project management committee. Family carers were the source of all information on the CHOICE leaflet and helped write it.

**7. Procedure (see Figure 2 Gantt chart timeline)**

We will begin by recruiting GP practices from the intervention and finalise Research and Development approval (explained fully in ethics section). We already have three local practices and two memory services engaged. [name] will visit clinical settings individually to discuss the study. We will start to engage commissioners and recruit more memory services, asking them to plan to make this intervention if successful part of usual practice. We will discuss the possibility of extra workload requiring funding although this should be small for any individual clinic.

Recruitment will continue as the pragmatic, multi-site, cluster randomised controlled trial begins. Clustering will be by practices. We will send the intervention to people aged over 70 years in the included practices. Many or most of those will either know someone with a diagnosis of dementia or themselves have symptoms. We will exclude those with an existing diagnosis of dementia or referral to memory services, and those living in care homes (as most will already have a diagnosis). The intervention’s effectiveness will be evaluated using routinely collected data. Data will be collated at baseline, 3, 6 and 12 months after the letters are sent. The leaflets are available on the internet and we will not try to influence GPs use of them in the usual practice group.

**8. Data collection**

All data will be anonymised and collected for intervention and control practices. Consent will be through cluster guardians32, who will provide consent for collection of this data33.

1. Sociodemographic data about the person with suspected dementia will include gender, age, ethnic status according to census, marital status, education, living situation and location. We will record GP characteristics and practice size.
2. **The primary outcome** is the cognitive score as measured by the Mini Mental State Examination (MMSE)34 of people referred to memory services in the intervention and control groups who receive a diagnosis of dementia. The minimum clinically important difference in MMSE score is three points2 and is the most widely used standard test of cognitive function34. We will collate the baseline MMSE score from the new patients’ presenting to memory clinic (i.e. MMSE scores of new presentations) at 3, 6 and 12 months after sending the letters. We are not collecting follow-up MMSEs. There is a maximum score of 30, with scores of 0-10=severe, 11-20=moderate, and 21-24=mild dementia35.
3. **Secondary outcomes**

- Number of people presenting with a possible diagnosis of dementia will be collected from GPs practices using MiQUEST36 (a Department of Health computer system allowing anonymised data extraction from GP practices). [name] is an expert in using this and is one of the project team. We will collect the number of people presenting to their GP who are and who are not referred on to memory services.
- Numbers of patients referred to memory services from participating intervention and control practices
- The number of memory services appointments offered and people attending for diagnostic assessment,
- The number of people referred who do not have dementia or mild cognitive impairment
- Costs of implementing the intervention, including the costs associated with the CHOICE leaflet (printing, and distribution), GP visits to discuss possible diagnoses of dementia, and use of memory services, and the cost of assessing those with and without dementia
- We will systematically ask clinicians about any inappropriate presentations and patient distress and record these as adverse events.

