**9. Power calculations and statistical methods to be used**

Sample size

Approximately 14% (1 in 7) of people aged >70 have dementia37. The average GP registered patient population is ≈200038, of whom 260 (13%)39 are ≥70 years old. Thus there is a mean of 36-37 patients with dementia per GP of whom 24 would be unknown. An audit of people with dementia presenting to Islington memory services showed a mean MMSE score =19.5 (standard deviation=6.1). A clinically significant difference between experimental and control arms =3 points in MMSE2. To achieve this would require 71 undiagnosed people with dementia in each group (=5% and power=90%). In Islington last year 420 patients were referred from the 38 practices – a mean of 11/practice. Since families in group practices may receive the intervention letter from one GP then consult and be referred by another, cluster randomisation is appropriate and will be used to allocate GP practices to the intervention or control arms. Consequently, we need to inflate the sample based on a projected intracluster correlation of 0.0340. The required sample size in each arm is then 93. This will equate to 8580 people aged over 70 registered with the GPs. If 11 patients are referred per practice, we require approximately nine practices (clusters) in each trial arm. The primary outcome is routinely collected data; but some patients will become too ill or die, or refuse assessment by the clinics. Estimated level of attrition rate=18% (18% loss to follow up in LASER including deaths- a previous dementia study in the community), and therefore we aim to recruit 11 GP practices in each arm. Randomisation will be computerised and stratified by geographical location. The allocation ratio will be 1:1.

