**10. Analysis**

We will report descriptive sociodemographic and clinical data by randomisation group. We will conduct between group comparisons for categorical and linear data. We will compare the mean MMSE from each group and will use t-tests or Mann-Whitney where appropriate. Statistical modelling will be performed in the form of hierarchical multivariate regression analysis, to account for clustering of patients. Analysis of covariance (ANCOVA) will be used to adjust for baseline differences in outcome variables and multiple linear regression will be used to identify other predictors of MMSE at presentation e.g. gender, age and ethnicity. In the regression analysis we will account for the clustering effect in suitable ways (e.g. random effects models). We plan to perform a primary analysis on complete cases and then develop secondary analyses adjusting for potential missing data using suitable methods (e.g. multiple imputations, and inverse probability weighting). We will apply these as sensitivity analysis and discuss them in conjunction with the main analysis. Missing data is accounted for in the sample size calculations; thus we should be able to observe enough complete cases to preserve the power for the main analysis. For the cost analysis the costs associated with printing and distributing the CHOICE leaflet will be based on market prices. Numbers of GP visits will be taken from MiQUEST29 and numbers of contacts with memory services will be taken from practice records. All contacts will then be costed by applying unit costs from published sources41. We will then calculate and compare the mean cost of delivering the intervention per patient and the use of GP and memory services in each arm.

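### Mean MMSE among the diagnosed mixes earlier timing with a changed case mix, because the letter is meant to alter who is diagnosed

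*Protocol*

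**What the plan says.** Section 4 defines the population through the practice lists: "We will include all registered patients within GP practices over the age of 70 years", leaving out people with a dementia diagnosis, care-home residents and those already referred to memory services. Section 9 says that cluster randomisation "will be used to allocate GP practices to the intervention or control arms".

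The primary outcome in section 8 is narrower than that population. It is the MMSE "of people referred to memory services in the intervention and control groups who receive a diagnosis of dementia". Each person contributes a single score taken at first presentation to the memory clinic, and "We are not collecting follow-up MMSEs". Section 10 states "We will compare the mean MMSE from each group", supported by regression that allows for clustering.

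Section 1 makes earlier diagnosis the primary objective and expresses it as a mean MMSE 3 points higher. Its first two secondary objectives are "To increase the number of people with dementia receiving diagnoses" and "To increase the numbers of people with memory problems presenting to GPs". Section 9 describes the pool from which further diagnoses could come: "Thus there is a mean of 36-37 patients with dementia per GP of whom 24 would be unknown".

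The secondary outcomes in section 8 include presentations, referrals, appointments and attendances, and referred people with neither dementia nor mild cognitive impairment. The number diagnosed with dementia is not itself listed, and no count is combined with MMSE.

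**The concern.** A person enters the primary analysis only by presenting, being referred and being diagnosed after the letters go out. The letter is meant to affect all of these steps. Randomisation makes the practices and their eligible lists comparable. It does not make the people diagnosed in one arm comparable with those diagnosed in the other.

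The trial's own objectives can pull the mean apart. Bringing usual presenters forward raises it. Finding people who would otherwise have stayed undiagnosed lowers it when they score below the rest and raises it when they score above. A letter that succeeds on both objectives could show a small difference. A letter that only adds mild cases could show a positive one without bringing forward anyone who would have presented during the year. The mean alone cannot tell these apart.

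The adjustments in section 10 do not reach this problem. ANCOVA for baseline values of the outcome has nothing to work with, since no one has an MMSE from before the letter. Multiple imputation and inverse probability weighting are offered for missing data, but undiagnosed people have no record in the outcome data to impute or weight from.

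**Working it through.** **The plan's own sample size.** Inputs from section 9: difference 3, SD 6.1, 5% significance, 90% power, ICC 0.03, 11 referred per practice, 18% attrition.

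- n per arm = 2 × (1.645 + 1.282)² × 6.1² / 3² = 70.8, so 71. This matches the protocol with a one-sided 5% test; a two-sided test gives 87. The protocol does not state sidedness, so both are shown below.
- Design effect = 1 + (11 − 1) × 0.03 = 1.30; 71 × 1.30 = 92.3, so 93.
- 93 / 11 = 8.45, so 9 practices; 9 / 0.82 = 10.98, so 11 practices per arm.

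The chain reproduces. It uses 11 per practice in both arms, so it makes no allowance for a change in who is diagnosed.

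**Precision as designed.** With 11 practices per arm and 11 × 0.82 = 9.02 analysed per practice:

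SE = √[2 × (0.03 × 37.21 + 0.97 × 37.21 / 9.02) / 11] = √[2 × (1.116 + 4.002) / 11] = 0.965.

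**Masking.** Assume that usual presenters gain the full 3 points (19.5 to 22.5), that 11 per practice are diagnosed, and that the letter adds k cases per practice with mean MMSE m. Section 9's figure of 11 is referrals, so using it for diagnoses is an assumption. So are k and m.

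Observed difference = (11 × 22.5 + k × m) / (11 + k) − 19.5. Power = Φ(difference / 0.965 − 1.96), or − 1.645 for one-sided.

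| k | m | Difference | Power, two-sided | Power, one-sided |
|---|---|---|---|---|
| 0 | – | 3.00 | 88% | 93% |
| 1 | 16 | 263.5/12 − 19.5 = 2.46 | 72% | 82% |
| 2 | 16 | 279.5/13 − 19.5 = 2.00 | 55% | 67% |
| 5 | 16 | 327.5/16 − 19.5 = 0.97 | 17% | 26% |
| 8 | 16 | 375.5/19 − 19.5 = 0.26 | 5% | 8% |

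With 5 extra cases, m = 14 gives 0.34 and m = 18 gives 1.59. Allowing for the larger intervention clusters moves the 17% to about 19%.

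Write r for the proportional rise in diagnoses. The difference vanishes when m = 19.5 − 3/r. That is 13.5 for a 50% rise and 16.5 for a doubling, both inside section 8's moderate band (11-20). For a 10% rise it is −10.5, which is impossible, so a small rise dilutes the difference but cannot cancel it.

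**The opposite error.** With usual presenters unchanged at 19.5, the difference is r × (m − 19.5) / (1 + r).

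- 50% more cases at 24: 0.5 × 4.5 / 1.5 = 1.5.
- 100% more at 25.5: 6.0 / 2 = 3.0. This mean lies above the top of section 8's mild band (21-24).
- At a mean of 24, prompted cases would have to be 3 / 4.5 = two-thirds of all diagnoses to give 3 points.

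**The case against.** The strongest reply is that mean severity among a practice's new diagnoses is itself a practice-level outcome, and section 3 sets out to compare exactly that. Its contrast between randomised practices is then an effect of the letter. A prompted mild case who would otherwise have been diagnosed years later is also an earlier diagnosis, so changed case mix is partly the intended mechanism. This stands as far as it goes. A reader might infer that the trial has no randomised comparison at all, and the documents do not support that. What is not protected is the reading of the mean difference as a shift in timing among comparable people.

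The size is also open to challenge. Nothing in the protocol says how many extra cases the letter would find or how severe they would be, and one or two extra per practice leave most of the difference intact. A reader might infer that the primary result is bound to be null, or that most of a 3-point difference must come from case mix. The first needs a large rise in lower-scoring cases. The second needs a rate of MMSE decline that the protocol does not give.

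A reader might also take the descriptive table by arm as a mistaken proof of baseline balance. It does describe a group formed after randomisation, but section 10 only promises to report it and claims nothing about balance.

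Finally, the secondary counts and section 8's severity bands help interpretation, and a supporting model could sit in an analysis plan that is not shown. However, the protocol itself fixes the outcome, its population and the comparison of means. The listed counts neither include dementia diagnoses nor link to MMSE.

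**Conclusion.** The point holds. The primary analysis conditions on being diagnosed, an event after randomisation that the letter is designed to change, and no analysis in the protocol separates earlier timing from altered case mix. The error can run either way, so a null and a positive result both need more information before they are read as evidence on earlier diagnosis.

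The size cannot be derived from the documents. Under the stated assumptions, extra cases at MMSE 16 reduce a true 3-point gain to between 2.5 (1 extra per practice) and 0.3 (8 extra). Full cancellation needs something like 50% more cases at 13.5 or 100% more at 16.5. A spurious 3 points needs a doubling at 25.5 or a tripling at 24. These figures illustrate the mechanism and do not predict the result.

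**What to change.** Keep mean MMSE as the primary outcome. State in section 10 that it is conditional on diagnosis and reflects both timing and case mix.

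Add one named key supporting analysis: first dementia diagnoses over 12 months with MMSE 21 or more, and separately 20 or less, per eligible over-70 on each practice list. Fix the lists before randomisation in both arms. Compare arms with a practice-level count model that allows for over-dispersion, with log list size as offset. Interpret the mean alongside the two rates. A rise in the upper band with little change in the lower has a different meaning from a rise in both.

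Do not make the claim of earlier diagnosis depend on a significant rise in the upper-band rate. Take a pure 3-point shift with no extra cases, normal scores with SD 6.1, a cut at 20.5 and 11 diagnosed per practice. The upper-band count then goes from 11 × 0.435 = 4.8 to 11 × 0.628 = 6.9 per practice. Over 11 practices per arm, Poisson power is about 54% two-sided before any over-dispersion, so such a rule could reject a true effect. Requiring both results would also leave the masking case null, because the mean would still be null.

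The cost is protocol wording, one extra model and an eligible-list count from control practices. Intervention practices need that list for the mailing anyway, and the primary analysis already needs MMSE, diagnosis and practice. The rates are less precise than the mean when the effect is a pure shift in MMSE.

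### Mean MMSE is compared only among people referred and diagnosed after randomisation, a group the intervention is meant to change, so it cannot by itself show earlier diagnosis; no listed outcome counts dementia diagnoses

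*Protocol*

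**What the plan says.** **Population.** Section 4 takes in everyone eligible on the practice lists: "We will include all registered patients within GP practices over the age of 70 years who do not currently have a diagnosis of dementia", with care-home residents and people already referred to memory services also excluded. Practices are randomised 1:1 (section 9).

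**Primary outcome.** Section 8 takes the MMSE of "people referred to memory services in the intervention and control groups who receive a diagnosis of dementia". There is one score per person, at first presentation to the memory service: "We are not collecting follow-up MMSEs". The severity bands given there include "11-20=moderate, and 21-24=mild dementia".

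**Inference.** Section 1 equates the score with timing. The hypothesis is that "over 12 months people receiving the intervention will present earlier (mean of 3 points higher on MMSE score" than people who do not receive it.

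**Aims.** Section 1 also sets out to test whether the intervention "increases the number of people with undiagnosed dementia presenting with memory related problems to their GP" and whether GPs make more appropriate referrals. Secondary objective 1 is "To increase the number of people with dementia receiving diagnoses".

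**Secondary outcomes.** Section 8 lists GP presentations (referred on or not), referrals, appointments offered and attended, referred people with neither dementia nor mild cognitive impairment, costs and adverse events.

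**Analysis.** Section 10 compares mean MMSE between arms, allows for clustering in regression models and uses complete cases first. Multiple imputation and inverse probability weighting are sensitivity analyses for missing data.

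**The concern.** Membership of the analysed group is decided after randomisation, by events the letter and leaflet are designed to influence. If the intervention works as intended, the diagnosed patients in the two arms are different kinds of people. The difference in mean MMSE then has two sources: people who would have been diagnosed anyway arriving earlier, and additional people, milder or more impaired, entering the average.

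Nothing in section 10 separates the two. Covariance adjustment for baseline cannot do so, because no individual MMSE from before presentation is described. Imputation and weighting are aimed at missing data, not at who is referred and diagnosed.

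The more serious risk is a false null or a reversed result. An intervention that brings usual presenters forward and also uncovers long-undiagnosed, more impaired people could be reported as ineffective or harmful. The outcome that would reveal this, the number of dementia diagnoses in the randomised population, is an objective without a listed outcome.

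**Working it through.** **1. The plan's own figures.** Section 9 gives a mean of 19.5, SD 6.1, target difference 3, 5% significance, 90% power, intracluster correlation 0.03 and 11 referrals per practice.

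- Before clustering: n = 2 × (1.645 + 1.282)² × 6.1² / 3² = 70.8, so 71 per arm, as stated. This reproduces with a one-sided 5% test; a two-sided test gives 87. That is a separate matter.
- Design effect: 1 + (11 - 1) × 0.03 = 1.30.
- After clustering: 71 × 1.30 = 92.3, so 93 per arm, as stated.

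The calculation uses the same 11 per practice in both arms. It makes no allowance for a change in the number or mix of people diagnosed.

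**2. Formula for the mixture.** Let *u* be the number per practice who would be diagnosed anyway, with mean μ in the intervention arm. Let *k* be the number of extra people found, with mean *m*. Then

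difference = (u·μ + k·m) / (u + k) - 19.5.

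Only 19.5 and the 3-point target come from the protocol. The values of *k* and *m* are assumed and shown as a range. Only the ratio k/u matters to the result.

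**3. The intervention works for usual presenters (μ = 22.5).**

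| Extra cases | m = 14 | m = 16 | m = 18 | m giving zero difference |
|---|---|---|---|---|
| k = u/2 | +0.17 | +0.83 | +1.50 | 13.5 |
| k = u | -1.25 | -0.25 | +0.75 | 16.5 |

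For example, with k = u and m = 14: (22.5 + 14)/2 - 19.5 = -1.25. The zero-difference value is m = 19.5 - 3u/k.

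**4. Timing of usual presenters unchanged (μ = 19.5).** A 50% rise in diagnoses means extra cases are one third of the total, so the shift is (m - 19.5)/3.

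- m = 24: +1.5.
- m = 15: -1.5.

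**5. What dilution does to power.** With 93 per arm, the effective number is 93/1.30 = 71.5 and the standard error is 6.1 × √(2/71.5) = 1.02. Power = Φ(difference/1.02 - 1.645), one-sided.

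- Difference 3: 0.90.
- Difference 1.5: 0.43.

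The two-sided figures are 0.84 and 0.31. These hold the analysed number at 93 per arm; extra diagnoses would enlarge the intervention arm and soften the loss somewhat.

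**6. Whether the listed outcomes fill the gap.** Subtracting referred people with neither dementia nor mild cognitive impairment from those assessed leaves dementia and mild cognitive impairment combined. The secondary outcomes therefore give no count of dementia diagnoses, and none is expressed per eligible patient.

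**The case against.** The strongest defence is that the sponsor asked about severity at diagnosis (section 3) and chose an outcome that measures it. Presentations, referrals and attendances will show whether volume changed. The number diagnosed is available as the size of the primary-outcome dataset. Reading the mean alongside the counts could be left to a statistical analysis plan, which is not shown.

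Part of this stands. The outcome does suit the question, and the counts help. But the outcome definition and the list of outcomes are fixed in the protocol. The dataset size is not named as an outcome, nor tied to a denominator, although more diagnoses is a stated objective.

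Four stronger readings are tempting and are not supported:

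- **That the outcome is averaged only over people the intervention causes to be referred.** Section 8 takes new diagnosed referrals from both arms, including people who would have presented anyway. The accurate statement is that membership is affected by the intervention.
- **That extra mild cases make a false positive.** Someone diagnosed at a mild stage who would otherwise have been found later, or never, is arguably a genuine earlier diagnosis.
- **That a 3-point difference is very hard to reach.** This holds only if the timing of usual presenters is unchanged. The leaflet deals with persuading a person to attend, a doubtful GP and obtaining referral, any of which could bring usual presenters forward. If they come 3 points earlier and no extra cases are found, there is no dilution.
- **That a co-primary outcome is required.** It would need its own power and multiplicity provisions. A key secondary outcome meets the need.

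**Conclusion.** The point holds in this form: the difference in mean MMSE among diagnosed patients is not protected by randomisation and cannot by itself show earlier diagnosis. A higher mean is compatible with earlier diagnosis but does not identify it; a null or lower mean is compatible with success.

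On the protocol's own mean and target, a 3-point benefit to every usual presenter is fully cancelled if an equal number of extra cases averages 16.5, or if half as many average 13.5. Whether this would happen cannot be settled from the protocol. Section 9 puts 24 of 36-37 people with dementia per GP as unknown, so there is a pool to find, but its severity is not stated. The size and direction of the distortion therefore rest on assumed numbers and severities.

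The selection itself, and the absence of a diagnosis count to match secondary objective 1, need no assumption. This is a reason to support the primary outcome with another measure, not to replace it.

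**What to change.** Keep mean MMSE as the primary outcome.

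**Section 8.** Add as first key secondary outcome: new memory-service dementia diagnoses over 12 months per 1,000 eligible registered patients aged over 70. Fix the denominator at randomisation in both arms, using the section 4 criteria. Report the rate overall and split at MMSE 21 or above against 20 or below, which is the protocol's own boundary between mild and moderate. Analyse it allowing for clustering by practice.

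**Section 10.** State that the mean MMSE difference is interpreted together with these rates:

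- A higher mean is read as earlier diagnosis only if the rate at MMSE 21 or above also rises. This guards against a mean that rose only because fewer severe cases were diagnosed.
- A null or lower mean with a higher diagnosis rate is not read as failure of the intervention.

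**Cost.** One more analysis and a more cautious conclusion. The denominator needs a count of eligible patients in control as well as intervention practices; section 8 mentions only practice size, but MiQUEST extraction from practices is already planned. Diagnosis and MMSE are already collected. Because the new outcome is not co-primary, the sample size and the primary test stay as they are.
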